### Primary and secondary outcome measures

#### Primary outcome

The primary endpoint is the change in ADHD symptoms from T2 to T3 measured by changes in the total score of the Diagnose-Checkliste für Aufmerksamkeitsdefizit−/Hyperaktivitätsstörungen (DCL-ADHS), a structured DSM-5-based clinical interview. It comprises 18 items assessing ADHD symptoms, and five items assessing functioning and psychological strain and shows good internal consistency (Cronbach’s α = 0.89–0.95) and high validity [52–54]). All items are rated on a 4-point scale (0–3; symptom present if ≥2). For ESCAadol, the interview is conducted with parents and adolescents in a joint session.

#### Secondary outcomes

The most important secondary endpoint is the change on the Clinical Global Impression Scale (CGI, [51]) from T2 to T3 and from T2 to T4. It measures the severity of the disease (CGI-S) and the general improvement through treatment (CGI-I). The assessment takes place after a short clinical interview. CGI-S and CGI-I are evaluated on a 7-point scale, with higher scores indicating a greater severity or impairment, respectively. Despite conflicting findings with regard to reliability and validity, the CGI is widely used in clinical trials as an outcome parameter. The CGI-I shows good interrater reliability (0.65–0.92) [55] and an intra-class correlation coefficient of 0.91 [56].

Further secondary endpoints are changes in patient-, parent- and teacher-rated ADHD and symptoms of oppositional defiant disorder (ODD) and conduct disorder (CD), ADHD-related functional impairment and quality-of-life, internalising and externalising symptoms and parenting from T2 to T3, and T2 to T4:

#### ADHD and ODD/CD symptoms

Parents, teachers and patients rate the severity of all of the core symptoms of ADHD and a core set of symptoms of CD on a 4-point scale on the questionnaires *Fremdbeurteilungsbogen für Aufmerksamkeitsdefizit-/Hyperaktivitätsstörungen* (FBB-ADHS; parent report Cronbach’s α = 0.91–0.94; teacher report Cronbach’s α = 0.87–0.93), *Selbstbeurteilungsbogen für Aufmerksamkeitsdefizit-/Hyperaktivitätsstörungen* (SBB-ADHS; self-report; Cronbach’s α = 0.79–0.89), *Fremdbeurteilungsbogen für Störungen des Sozialverhaltens* (FBB-SSV; parent report Cronbach’s α = 0.67–0.91; teacher report Cronbach’s α = 0.69–0.92) and *Selbstbeurteilungsbogen für Störungen des Sozialverhaltens* (SBB-SSV; self-report [52]; Cronbach’s α = 0.65–0.89). The Diagnose-Checkliste für Störungen des Sozialverhaltens (DCL-SSV) will be completed by a semi-blinded clinician rater based on an interview with parents and adolescents [52]. This interview also shows good internal consistency (Cronbach’s α = 0.68–0.88).

#### Functional impairment and quality of life

The *Weiss Functional Impairment Rating Scale* (WFIRS-P, [57, 58]) assesses impairment specifically associated with ADHD. Parents rate 40 items on the dimensions family, learning and school, life skills, child’s self-concept and social activities on a 4-point scale. This interview also possesses good internal consistency (Cronbach’s α > 0.7), test-retest reliability (*r* > 0.7) and validity [59, 60]. The *Health-Related Quality of Life Questionnaire for Children and Young People* (KIDSCREEN-10, [61, 62]) comprises 10 items and measures the parent- and child-rated subjective health and well-being of children and adolescents on a 5-point scale. The authors report good internal consistency (Cronbach’s α = 0.82) and test-retest reliability (*r* = 0.73).

#### Internalising and externalising symptoms

The *Child Behaviour Checklist* (CBCL/6-18R) is a parent questionnaire assessing the behavioural and emotional problems of children and adolescents with 113 items on a 3-point scale. The instrument shows good reliability for most scales (rtt > .80) and good validity [63–65].

#### Parenting Rating Scales

Perceived parenting sense of competency concerning difficult parenting situations is assessed with the questionnaire *Verhalten in Risikosituationen* (VER [66]). The first 14 items describe typical situations (e.g. going shopping). Thirteen other items describe child behaviour (e.g. ‘refuses to eat’). On a 4-point scale, parents can state how well they can manage the situations. Positive parenting will be assessed with the *Fragebogen zum Erziehungsverhalten* (FZEV), which has been devised using items from the Positive Parenting subscale of the *Parent Practices Scale* (PPS [67]) among others. It consists of 13 items which measure positive, reinforcing and encouraging parental behaviour such as praise, playing together, attention and physical affection on a 4-point scale. Both instruments show good internal consistency [67, 68] and have been used in multiple intervention studies; e.g. [69]. Negative parenting is measured by a short version of the negative parenting subscale of the German questionnaire *Fragebogen zum positiven und negativen Erziehungsverhalten* (FPNE [70]. The questionnaire consists of 13 items with a 4-point scale.

### Therapy preconditions and process variables

To gain insight into motivational aspects for treatment as well as treatment quality, measures of treatment expectation, motivation and satisfaction ratings of participating parents and the adolescents are included. Therapists will rate their treatment expectation as well as provide data regarding treatment integrity and adherence. Furthermore, we will examine changes in the concentration of genetic transcripts such as micro-RNAs and mRNAs in peripheral tissue as potential biological correlates of response to therapy pre- and post-treatment.

### Predictors and moderators of therapeutic outcome

#### Predictors – Psychometric data

As possible predictors of the primary treatment outcome, we will collect data with regard to sociodemographic information (e.g. age and sex, IQ, familial psychosocial risk factors) and treatment expectation of the parent, adolescent and therapist.

Furthermore predictors comprise child temperament (*Junior Temperament and Character Inventory,* JTCI; parent- and self-report; test-retest reliability *r* = 0.65–0.87; Cronbach’s α = 0.79–0.85; validity [71–73]), emotional dysregulation (adolescent self-report on the German questionnaires *Fragebogen zur Erhebung der Emotionsregulation bei Kindern und Jugendlichen,* FEEL-KJ; test-retest reliability *r* = 0.62–0.81; Cronbach’s α = 0.69–0.91; validity [74, 75]), and social responsiveness of the child (*Social Responsiveness Scale,* SRS; test-retest reliability *r* = 0.72–0.91; Cronbach’s α = 0.91–0.97; validity [76–79]), problem behaviour on various domains according to the *Youth Self Report Scale* (YSR; good test-retest reliability internal consistency and validity [80–82]) and irritability (*Affective Reactivity Index,* ARI; test-retest correlation *r* = 0.88 for parent-report and 0.29 for self-report; Cronbach’s α = 0.89 for parent-report and 0.90 for self-report [83]; validity [84]).

Furthermore we assess parental variables such as ADHD (*ADHS-Selbstbeurteilungsskala* ADHS-SB: test-retest reliability *r* = 0.78–0.89; Cronbach’s α = 0.72–0.9, validity [85]*; Wender Utah Rating Scale – deutsche Kurzform,* WURS-K: test-retest reliability *r* = 0.9; Cronbach’s α = 0.91, validity [85, 86]), depression, anxiety and stress (*Depression Anxiety Stress Scales,* DASS; Cronbach’s α = 0.89–0.96, test-retest realability *r* = 0.71–0.81, validity [87, 88]) as well as parental coping with anger (*Elternfragebogen zum Umgang mit Ärger*, FB-Ä [89]) with self-report questionnaires. As a further predictor, clinical rating scores on psychiatric comorbidity in the child obtained with the structured screening interview *Diagnose-Checkliste zum Screening psychischer Störungen* (DCL-SCREEN*,* [52]) will be used. In this study, the DCL-SCREEN will be used to screen for symptoms of autism spectrum disorders, depressive disorders, anxiety disorders, obsessive-compulsive and related disorders, tic disorder, somatoform and related disorders, motor and language disorders, specific learning disorders and elimination disorders. In case of clinical symptoms emerging in the *DCL-SCREEN*, we will use the diagnostic checklist for the particular disorder from the *Diagnostik-System für psychische Störungen nach ICD-10 und DSM-5 für Kinder- und Jugendliche* (DISYPS-III*,* [52]) for an extensive assessment based on DSM-5 diagnostic criteria.

#### Predictors – Biological variables

The selected predictors will be obtained through assessments with electroencephalography (EEG; spontaneous and event-related EEG-recordings), magnetic resonance imaging (structural MRI, diffusion tensor imaging and functional MRI) as well as transcranial sonography (TCS). Furthermore, blood and saliva samples will be collected from all participants before (T1) and after treatment (T3). EEG and MRI measurements are limited to the subgroup receiving the IMTP and will be performed following randomisation. TCS measurements will be performed at any time during the study with all patients who provide informed consent.

TCS is a non-invasive method for the visualisation of deep brain structures through the intact skull. Ultrasound waves are reflected depending on tissue composition, resulting in different echogenicity of nuclei and ventricular system. Of particular interest is the mesencephalic scanning plane including brainstem, substantia nigra and raphé nuclei. In children, ADHD-associated hyperechogenicity of the substantia nigra has consistently been reported and it has been proposed as a potential biological marker for ADHD [90, 91]. TCS can aid differential diagnosis (e.g. in movement disorders, [92]) and has shown promise in the prediction of treatment response in psychiatric disorders in adult patients [93, 94]. As of yet, no study has explored the possibility of using TCS to predict the effectiveness of non-pharmacological interventions. In the context of our study, the TCS-based predictor of treatment outcome will be the size of the echogenic area of the substantia nigra, which has been shown to be associated with the disorder [90, 91].

Genetic material will be extracted from blood and saliva samples. We will analyse genetic variants in candidate gene systems for their predictive value regarding an individual’s response to different therapeutic interventions.

The EEG-based predictors consist of the frequency profile at rest (spontaneous theta-band and alpha-band activity) and the strength of preparatory cognitive activity (contingent negative variation amplitude), which explain nearly 30% of the variability in behavioural improvement following neurofeedback treatment [95]. To test the mechanisms of improvement underlying the IMTP, EEG recordings are repeated following this treatment in step 2. The changes in brain electric activity, i.e. the hypothesised reduction of resting theta-activity and increased contingent negative variation activity, will be treated as additional secondary outcome measures in this subgroup.

The MRI-based predictors consist of the integrity (fractional anisotropy) of the fronto-striatal connection and of volumetric grey matter density of the implicated dorsolateral-prefrontal und striatal regions.

As neuropsychological predictors we include four computer-based experimental paradigms: The *continuous performance task* (CPT-OX, [96]) measures selective attention and impulsive behaviour by requiring participants to withhold a prepared response through inhibitory response control. The *monetary incentive delay task* (MID, [97, 98]) is a paradigm to study reward anticipation and reward feedback in an event-related task with three task conditions (no win; small win; big win). The S*top Signal Task* (SST, [98, 99]) is used to study inhibitory control. The task composes go-trials and stop-trials. A tracking algorithm changes the time interval between go-signal and stop-signal onsets according to each subject’s performance on previous trials.

#### Moderators

For the investigation of moderators of treatment outcome, we will examine the influence of age, sex, socioeconomic status, ADHD symptom severity, comorbid symptoms, intelligence, parental mental health (parental depression, anxiety and stress assessed by self-ratings on the DASS; parental ADHD assessed with the ADHD-SB).

For an overview of all measures used at individual time points throughout the study, please refer to Fig. 2.

**Fig. 2 Fig2:**
[figure not shown]
Overview of outcome measures, predictors and eligibility criteria. Rater: *A* = adolescent, *B* = blind rater, *C* = clinician, *F* = father, *M* = mother, *P* = parents, *T* = teacher, *Th* = therapist; Variable type: *I* = inclusion criterion, *O* = outcome variable, *P* = predictor, *Q* = variable for quality control; Interventions, *IMTP* = Individualised Modular Treatment Programme, *TASH* = telephone-assisted self-help; measures: *ADHS-SB* = ADHS-Selbstbeurteilungsskala, *ARI* = Affective Reactivity Index, *CBCL* = Child Behaviour Checklist, *CGI* = Clinical Global Impression, *DASS* = Depression Anxiety Stress Scales, *DCL-ADHS* = Diagnose-Checkliste für Aufmerksamkeitsdefizit−/Hyperaktivitätsstörungen, *DCL-SCREEN* = Diagnose-Checkliste zum Screening psychischer Störungen, *DCL-SSV* = Diagnose-Checkliste für Störungen des Sozialverhaltens, *EEG* = electroencephalogram, *FAI* = Family Adversity Index, *FB-Ä* = Elternfragebogen zum Umgang mit Ärger, *FBB-ADHS* = Fremdbeurteilungsbogen für Aufmerksamkeitsdefizit-/Hyperaktivitätstörungen, *FBB-SSV* = Fremdbeurteilungsbogen für Störungen des Sozialverhaltens, *FEEL-KJ* = Fragebogen zur Erhebung der Emotionsregulation bei Kindern und Jugendlichen, *FPNE* = Fragebogen zum positiven und negativen Erziehungsverhalten, *FZEV* = Fragen zum Erziehungsverhalten, *JTCI* = Junior Temperament and Character Inventory, *KIDSCREEN-10* = The Health-Related Quality of Life Questionnaire for Children and Young People, *MID* = Monetary-Incentive-Delay-Task, *MRI* = magnetic resonance imaging*, SBB-ADHS* = Selbstbeurteilungsbogen für Aufmerksamkeitsdefizit-/Hyperaktivitätstörungen, *SBB-SSV* = Selbstbeurteilungsbogen für Störungen des Sozialverhaltens, *SRS* = Social Responsiveness Scale, *SST* = Stop Signal Task, *TCS* = transcranial sonography, *VER* = Verhalten in Risikosituationen, *WFIRS-P* = Weiss Functional Impairment Rating Scale, *WURS-k* = Wender Utah Rating Scale – short version, *YSR* = Youth Self Report Scale. *only for patients randomised to one of the two treatment conditions

### Rater training

Semi-blinded clinicians and blinded raters will be trained in the assessment of ADHD, CD and comorbid conditions with the DCL-ADHS and DCL-SSV. After viewing and scoring a video recording of a diagnostic interview using the DCLs, their ratings will be compared to a ‘gold standard’ established by the authors of the DISYPS-III. The first three interviews with participants will be supervised by a certified rater. A reliability analysis will be conducted at the end of the study.

### Randomisation procedure

Central randomisation with a 1:1 treatment ratio will be performed by the CTU at the University Medical Centre Freiburg via fax, using block randomisation with variable block length to guarantee concealment of randomisation. Randomisation will be stratified by centre. The randomisation request form contains the following information: study-specific patient identification number, year of birth and the confirmation of ADHD > cut-off. The central randomisation office will review the patient’s details on the randomisation fax. If data on the fax are complete and appropriate, the randomisation will be performed by the central randomisation office. The patient will be entered in the randomisation list at the randomisation office, and the randomised treatment arm will be sent to the investigator by fax. The returned randomisation fax will contain the information entered by the investigator complemented by the information about the randomised treatment (IMTP or TASH).If the details on the randomisation fax appear to be incomplete or implausible, the central randomisation office will send a query fax to the investigator for clarification.

### Monitoring and safety

The monitoring is performed by the clinical research associates (CRAs) of the CTU. Adapted monitoring will be done according to Good Clinical Practice (ICH-GCP) and standard operating procedures (SOP) to verify that patients’ rights and well-being are protected, reported trial data are accurate, complete and verifiable from source documents and that the trial is conducted in compliance with the currently approved protocol/amendment, with ICH-GCP and with the applicable regulatory requirements to ensure safety and integrity of clinical trial data. Prior to the trial, a pre-trial visit by phone, a site initiation visit at each site and an investigators’ meeting are conducted in order to train and introduce the investigators and their staff to the trial protocol, essential documents and related trial specific procedures, ICH-GCP and national/local regulatory requirements. Additional training via telephone may be employed if necessary.

During the trial, the monitor will visit the site regularly depending on the recruitment rate and quality of data. During these on-site visits, the monitor verifies that the trial is conducted according to the trial protocol, trial specific procedures, ICH-GCP and national/local regulatory requirements. The presence of signed informed consents, the eligibility of patients, primary endpoint, treatment compliance and documentation will be verified by the monitor. The monitor is also performing source data verification to ensure that clinical trial data are recorded and documented in the source data and case report forms (CRFs) are complete and accurate. Extent of source data verification and monitor visit frequency will be adapted for individual sites in case of lack of data quality or a high number of protocol violations.

An independent Data Monitoring Committee (DMC) is formed by [name]. med. [name], [name]. med. [name] and [name]. med. [name]. The DMC will advise the trial sponsor on patient safety and measures to ensure the credibility and integrity of the ongoing trial.

### Stopping rules

Stopping rules for an individual patient include withdrawal of informed consent of parents / guardians or the patient, need for inpatient treatment or other reasons affecting the patient’s well-being in the case of continued trial participation or need for a different kind of treatment for health reasons according to the judgement of the attending physician. The Ethics Committee will be informed immediately in case of severe adverse events during the conduct of the trial. Global stopping rules for the trial or closing of a centre include emerging of data leading to a revision of the risk-benefit ratio, on-going failure of recruitment or repeated violations of the study protocol or standard GCP rules. For a decision on the termination of the trial or of closing a centre, agreement between PI, site investigators, DMC members, responsible Ethical Committee and the CTU Freiburg is intended.

### Proposed sample size and power calculations

The calculation of the sample size (software: STPLAN Version 4.3) is based on the primary endpoint ‘change in total score of DCL-ADHS from T2 (after TAU-stabilisation) to T3 (after experimental or control treatment; 12 weeks)’ using the two-sided t test with a power of 80% at a significance level of 5%. Studies on psychosocial interventions on the treatment of ADHD report effect sizes of about *d* = 0.8 [100], where *d* denotes the difference in the change score between the two randomised groups in standard deviation units. However, we have chosen a smaller effect size to calculate the sample size because recent meta-analyses referring to less biased outcome criteria such as assessments by clinicians report smaller effects of non-pharmacological interventions for the treatment of ADHD [22]. Furthermore, these effect sizes are based on trials with mostly waiting control group, thus, we expect our effects to be smaller. Additionally, in our highly affected clinical sample treatment effects might be less pronounced. A smaller effect size also accounts for the fact that the planned intention-to-treat approach might dilute the true expected effect – patients who discontinue therapy will be included in the primary analysis. We assume low to zero pre-post effects within our control group. Therefore, an effect size of *d* = 0.5 between groups seems realistic, and it is considered to be still clinically relevant. To detect a difference assuming the true effect size is *d* = 0.5, 64 patients with non-missing data per group are required (critical *t* = 1.98, *df* = 126). In order to account for the possibility that a few patients (8%) will have incomplete data at T3, in total 140 patients will have to be randomised. Studies on psychosocial interventions in ADHD children and their parents report attrition rates ranging from 5 to 20%. The study by Antshel et al. on CBT for adolescents with ADHD-symptoms unresolved by medication fits best with our intended sample. In this trial CBT adherence was good (all patients attended 13–16 sessions with half of the patients never missing an appointment and half missing between one and three appointments). Therefore, a rate of 8% with incomplete data at T3 seems conservative [23].

The sample size will provide sufficient power to handle the described imponderabilia of dropouts and incomplete data. Based on clinical experience we assume that about 10% of the patients will be improved after TAU-stabilisation, and, therefore, estimate that *N* = 160 need to be recruited at baseline to attain 140 randomisations. Based on our prior research on clinical trials in ADHD [33] we expect a 30% to 40% rate of screening failures. Thus, about *N* = 250 patients will need to be screened for study participation.

### Statistical analyses

All statistical programming for analysis will be performed with the Statistical Analysis System (SAS®).The primary analysis is based on an intention-to-treat approach. This means that the patients will be analysed in the treatment arms to which they were randomised, irrespective of whether they refused or discontinued the treatment or whether other protocol violations are revealed. The per-protocol (PP) population is a subset of the Full Analysis Set (FAS) and is defined as the group of patients that had no major protocol violations, received a predefined minimum dose of the treatment and underwent the examinations required for the assessment of the endpoints at relevant, predefined times. The analysis of the PP population will be performed for the purpose of a sensitivity analysis.

Safety analyses will be performed in the safety population. Patients in the safety population are analysed as belonging to the treatment arm defined by treatment received. Patients are included in the respective treatment arm, if treatment was started / if they received at least one dose of trial treatment.

#### Analysis of primary endpoint

The primary statistical analysis will be by intention-to-treat, so that all randomised patients will be analysed according to their allocated arm. Changes in the DCL-ADHS score from T2 to T3 and T2 to T4, respectively, will be evaluated in a linear regression model including treatment, centre, visit and the respective T2-baseline DCL-ADHS. Further covariates predictive of missingness will be included based on a pre-specified selection strategy to correct for potential bias arising from missing data. The primary treatment comparison of the change score at T3 will be based on least-squares means with a two-sided 95% confidence interval. Other possibly relevant covariates may be considered as well. Subgroup analyses will be conducted in an exploratory manner by inclusion of interaction terms in the linear regression model. They will focus on the analysis of patients’ and parents’ comorbidities. In addition, gender effects will be investigated as prognostic and predictive factors.

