**Methods/design:**

In step 1, 160 adolescents aged 12 to 17 years with a diagnosis of ADHD will undergo a treatment as usual (TAU) observation phase of 1 month. In step 2, those still severely affected are randomised to the intervention group with an Individualised Modular Treatment Programme (IMTP) or a telephone-assisted self-help programme for parents (TASH) as an active control condition. The IMTP was specifically designed for the needs of adolescent ADHD. It comprises 10 sessions of individual cognitive behavioural therapy with the adolescents and/or the parents, for which participants choose three out of 10 available focus modules (e.g. organisational skills and planning, emotion regulation, problem solving and stress management, dysfunctional family communication). TASH combines a bibliotherapeutic component with 10 counselling sessions for the parents via telephone. Primary outcome is the change in ADHD symptoms in a clinician-rated diagnostic interview. Outcomes are assessed at inclusion into the study, after the TAU phase, after the intervention phase and after a further 12-week follow-up period. The primary statistical analysis will be by intention-to-treat, using linear regression models. Additionally, we will analyse psychometric and biological predictors and moderators of treatment response.

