## Methods/design

### Study design and trial flow

Written informed consent for the main trial and all add-on investigations will be obtained by a senior member of the study team from all participating adolescents, parents and – if applicable – teachers. The study is designed as a randomised controlled, multi-centre trial. In *step 1* of the study, a planned number of *N* = 160 participating adolescents with ADHD will undergo a 4-week treatment-as-usual (TAU) phase with their attending physician in order to assess changes in ADHD symptoms in routine care. This is a strictly observational phase, all treatment decisions remain with the attending physician. At the end of the TAU phase, the study team will obtain information on which treatments have been implemented during TAU, followed by an assessment of ADHD severity and general impairment. Afterwards, an expected number of *N* = 140 patients, for whom routine clinical care has been proven to be insufficient and who still suffer from severe ADHD, will be randomised either to the IMTP or to TASH. Treatments will be administered over the course of 12 weeks (*step 2* of the study). Measurements will be taken at baseline (T0: screening of inclusion and exclusion criteria and assessment of ADHD symptoms; T1: baseline assessment comprising anamnestic information, pharmacological and non-pharmacological treatment history, additional information on comorbidity and parental self-ratings regarding child variables and own mental health), after the TAU phase (T2), after the treatment phase (T3) and 12 weeks after the end of the treatment (follow-up examination; T4). Patients failing to meet the severity criterion after TAU and not having entered the randomisation stage will also be invited for a follow-up appointment (T4) in order to monitor their progress in clinical routine treatment. Patients who drop out of the study will be encouraged to still participate in the next study visits for data collection. For an overview of the trial flow, please refer to Fig. 1. Clinical assessments of ADHD symptoms and comorbid psychopathology constituting outcome parameters will be completed by an experienced clinician who is blind to the patient’s assignment to treatment condition, but not to the time point (T0–T4). All randomisation decisions will be based on those semi-blinded ratings. All interviews will be recorded and subsequently a subsample will be rated by a blinded expert in order to validate the semi-blinded ratings by the clinician. Concerning safety of study participants, unblinding will not be necessary, since blinding is limited to outcome raters.

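### The primary model names only the T2 DCL-ADHS as a severity covariate; adding the earlier pre-randomisation rating (T0/T1) is an optional, nearly free gain in precision

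*Protocol article*

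**What the plan says.** **The endpoint and model.** Under Primary outcome, "The primary endpoint is the change in ADHD symptoms from T2 to T3 measured by changes in the total score of the" DCL-ADHS. Under Analysis of primary endpoint, the change "will be evaluated in a linear regression model including treatment, centre, visit and the respective T2-baseline DCL-ADHS". The same section adds covariates that predict missingness, chosen by a pre-specified strategy. It also allows other covariates, without naming or committing to any.

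**The earlier rating.** Study design and trial flow describes "T0: screening of inclusion and exclusion criteria and assessment of ADHD symptoms" and has clinician ratings of ADHD running from T0 to T4. It gives the observation of symptom change in routine care as the purpose of the treatment-as-usual phase, which needs a score before and after it. The abstract says: "Outcomes are assessed at inclusion into the study, after the TAU phase, after the intervention phase and after a further 12-week follow-up period". The Fig. 1 legend marks T1 to T4 as visits with outcome parameters.

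**The sample size.** Under Proposed sample size and power calculations, the effect size *d* "denotes the difference in the change score between the two randomised groups in standard deviation units". A two-sided t test at 5% with 80% power is used: "To detect a difference assuming the true effect size is *d* = 0.5, 64 patients with non-missing data per group are required". Allowing that "a few patients (8%) will have incomplete data at T3, in total 140 patients will have to be randomised".

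**The concern.** Each randomised patient should have two clinician ratings of ADHD severity before allocation, about four weeks apart. A single rating carries measurement error and short-term fluctuation. Two ratings usually describe stable severity better than one, and in a covariance model that lowers the residual variance of the T3 outcome.

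The section that fixes the primary model commits to the T2 score alone. The inclusion score could enter through the missingness covariates only if it happens to predict missingness, and through the open clause only if someone later chooses it.

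At stake is the width of the confidence interval for the T3 treatment difference. Validity is not at stake. A covariate named in advance also leaves less discretion in the primary analysis than an open permission does.

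**Working it through.** **1. Reproducing the plan's figure.** Inputs from the sample-size section: *d* = 0.5, two-sided 5%, power 80%. The noncentral t distribution gives 64 per group (power 80.1%, critical *t* 1.979 on 126 degrees of freedom). Then 128 / 0.92 = 139.1, so 140 randomised. Both stated figures reproduce. They rest on an unadjusted t test of the change score and do not depend on the inclusion rating.

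**2. Gain under equal correlation.** Assumptions: equal variance at each visit and the same correlation *r* between any two of T0/T1, T2 and T3. With unit variance, the residual variances at T3 are:

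- T2 only: 1 − *r*²
- T2 plus T0/T1: 1 − 2*r*²/(1 + *r*)
- ratio of the second to the first: (1 + 2*r*)/(1 + *r*)²

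The interval narrows by 1 − √ratio. The number of patients whom 128 would stand for under the T2-only model is 128/ratio.

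| *r* | Variance ratio | Variance cut | Interval narrower by | 128 patients act like |
|---|---|---|---|---|
| 0.3 | 0.947 | 5% | 3% | 135 |
| 0.5 | 0.889 | 11% | 6% | 144 |
| 0.6 | 0.859 | 14% | 7% | 149 |
| 0.7 | 0.830 | 17% | 9% | 154 |

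**3. Gain if correlation fades with time.** In general the ratio is 1 − *p*², where *p* is the partial correlation of T0/T1 with T3 given T2:

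*p* = (*r*03 − *r*23·*r*02) / √[(1 − *r*23²)(1 − *r*02²)]

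Examples with *r*23 = 0.6:

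- *r*02 = 0.6, *r*03 = 0.36 (first-order autoregressive decay): *p* = 0, no gain
- *r*02 = 0.7, *r*03 = 0.50: *p* = 0.140, ratio 0.980, a 2% cut
- *r*02 = 0.7, *r*03 = 0.55: *p* = 0.228, ratio 0.948, a 5% cut

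**4. Power on the protocol's own scale.** The protocol puts *d* in standard deviations of the change score, whose variance is 2(1 − *r*). Dividing this by the residual variances in step 2 multiplies *d*² by 2/(1 + *r*) for T2 only, and by 2(1 + *r*)/(1 + 2*r*) for both scores. Power at 64 per group:

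| *r* | *d*, T2 only | Power | *d*, both scores | Power |
|---|---|---|---|---|
| 0.3 | 0.620 | 94% | 0.637 | 95% |
| 0.5 | 0.577 | 90% | 0.612 | 93% |
| 0.6 | 0.559 | 88% | 0.603 | 92% |
| 0.7 | 0.542 | 86% | 0.595 | 92% |

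In the three fading examples, power starts at 88.1% and becomes 88.1%, 88.7% and 89.7%.

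**5. Effect of the severity screen.** A simulation selected patients on a CGI-like score correlated 0.7 with the ADHD rating, removing 35% at T0 and a further 10% at T2. These settings are assumptions, loosely guided by the protocol's 30–40% screening failures and 10% improved. The variance cut was 9%, 12% and 15% at *r* = 0.5, 0.6 and 0.7, slightly less than without selection.

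**The case against.** The strongest reply is that nothing here is wrong. Regression of change on treatment, centre and the last value before randomisation is valid, and it is at least as efficient as the t test used for sizing. Full covariate lists are commonly left to the statistical analysis plan. The protocol says that this plan was written before the first inclusion; it is not shown and may already name the inclusion score. The text also never names the DCL-ADHS at T0/T1, and Fig. 2, the overview of measures by visit, is not shown. All of this stands, and it limits the point to an optional refinement. What remains is that the protocol's own model statement names T2 and does not commit to the earlier rating.

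Three stronger readings are tempting, and the documents do not support them.

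- **The T2 score is compromised by selection or regression to the mean.** Under Participants, CGI-S ≥ 4 is applied at screening and again after the treatment-as-usual phase, so T0 is a selection visit too. Raters know the time point at every visit. Selection is on the CGI-S, not the DCL-ADHS, and precedes randomisation, so it creates no bias between arms. Step 5 shows that it does not enlarge the gain.
- **Power would rise from 80% to the mid-eighties.** The 80% belongs to the unadjusted t test. On the protocol's change-score scale, the planned T2-adjusted model already has about 86% to 90% at *r* = 0.5 to 0.7.
- **Precision is certainly lost.** The gain depends on correlations that the documents do not give, and it can be nil.

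**Conclusion.** The point holds as an optional efficiency gain. An ADHD rating before the treatment-as-usual phase is well supported by the text; that it is the DCL-ADHS total is a strong inference, because eligibility requires a structured interview for DSM-5 ADHD and the DCL-ADHS is described as one. The T2 score is the only severity covariate that the primary model names.

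The likely benefit is a 5% to 17% cut in residual variance if correlations between visits are about equal (0.3 to 0.7), and 0% to 5% if they fade. On the protocol's scale this is worth about 3 to 6 points of power in the equal-correlation cases from 0.5 to 0.7, about 1 point at 0.3, and under 2 points in the fading cases tried. These figures assume equal variances across visits and approximate normality. The sample size stands as stated.

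**What to change.** First confirm from the visit schedule that the DCL-ADHS total score is recorded at T0/T1. If it is, add one sentence under Analysis of primary endpoint, and to the statistical analysis plan if it is not already there: the T0/T1 DCL-ADHS total enters the primary model as a second fixed baseline covariate beside the T2 score. Name it outright, so that it does not depend on the open clause on other covariates. State how a missing T0/T1 value is handled, so that no randomised patient drops out of the analysis for that reason. Keep change from T2 to T3 as the endpoint and leave the sample size unchanged.

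The cost is one degree of freedom out of about 126, with no extra visit or patient. If the inclusion score adds nothing beyond T2, the loss is negligible: power stays at 88.1% in the no-gain example.
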